## **5 RANDOMIZATION**

Once informed consent has been provided, the investigator should obtain the result of the randomization. Based on the random number table without stratification or blocks, patients will be assigned to one of the two intervention groups (1:1 ratio): iTBS stimulation-first or sham stimulation-first group.

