The analysis will be conducted in the intention-to-treat (ITT) populations and repeated in the per-protocol (PP) populations to test the robustness. For the ITT population, missing data will be imputed using the last observation carried forward method. EEG analyses will be performed in patients with valid EEG data, and adjustments for multiple comparisons will be conducted using the false discovery rate method. Two-sided P-values < 0.05 were considered statistically significant. All statistical analyses will be performed using PASS 20.0 (NCSS, LLC, Kaysville, UT, USA), R version 4.3.0 and SPSS version 26 (SPSS Inc., Chicago, IL, USA).

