## **3 STUDY DESIGN**

This will be a randomized, double-blind, crossover trial. Patients will be randomly assigned to the iTBS stimulation-first group or the sham stimulation-first group after the 5-day baseline assessments. During each treatment session, patients will receive either active stimulation or sham stimulation once daily for 5 consecutive days. The two treatment sessions are separated by a 5-day washout period. Demographic, MRI, and clinical characteristics of the patients will be collected at enrolment. The CRS-R score will be assessed before and after every session of active and sham stimulation within 2 hours. 32-channel EEG will be performed 20 minutes before and after the first and after the fifth treatment sessions within 30 minutes. The analyses will compare the effects of iTBS and sham stimulation on the CRS-R score and EEG and assess the functional outcomes of all the participants 3 months and 6 months after enrolment.

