## **4 DETERMINATION OF SAMPLE SIZE**

We determined that enrolling 44 patients would provide 90% power to detect a mean difference of 1.2 points (standard deviation [SD] = 1.5) in CRS-R changes between the active and sham stimulation groups, using a two-sided  $\alpha$  of 0.05 and accounting for a 15% dropout rate. The anticipated  $1.2 \pm 1.5$ -point difference was conservatively estimated based on previous studies.

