## 6 EFFICACY ANALYSIS

Continuous variables will be expressed as mean  $\pm$  standard deviation (SD) or median (interquartile range, IQR), and categorical variables will be expressed as percentages. Baseline continuous variables will be analyzed using Student's t-test for normal distribution and Mann - Whitney U test for skewed distribution. Categorical variables will be analyzed using  $\chi^2$  test analysis and Fisher's exact tests, when appropriate.

Besides the primary and secondary outcomes mentioned above, we will conduct a post-hoc analysis of the changes in CRS-R scores and EEG after the first treatment session. At three- and six-months post-treatment, the consciousness of patients will be additionally assessed based-on CRS-R via telephone interview.

The between-group differences in the change of CRS-R total and subscale scores after the first and fifth treatment sessions will be analyzed using a linear mixed model (LMM) with fixed effects (sequence, period, time since injury, etiology, and age) and random effects (subjects for repeated measurements).

The effects of cerebellar iTBS on CRS-R total scores will be further analyzed in subgroups of patients according to their baseline characteristics, i.e., VS/UWS and MCS, as well as anoxia etiology and non-anoxia etiology.

The between-group differences in PSD after the first and fifth treatment sessions will also be analyzed via LMM, incorporating baseline PSD as a fixed effect alongside other fixed and random variables as above.

The cumulative link mixed effects model (CLMM), which incorporated fixed and random effects as those of LMM (fixed effects: sequence, period, time since injury, etiology, and age; random effects: subjects for repeated measurements) and added baseline "ABCD" EEG patterns as fixed effects, will be used to analyze the between-group differences in "ABCD" EEG patterns after the first and fifth treatments.

We will use the ordinal logistic regression to explore the relationships between the baseline "ABCD" EEG patterns and the functional outcomes and recovery of consciousness six months post-treatment. To investigate the relationships between EEG responsiveness and six-month outcomes, we will use the generalized linear model (GLM), with adjustments made for baseline characteristics and time period.

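### The plan analyses the iTBS effect in subgroups without a treatment-by-subgroup interaction, so it cannot show whether the effect differs between them

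*Supplement*

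**What the plan says.** The whole subgroup plan is one sentence, identical in SAP V2.0 section 6 (Efficacy Analysis) and protocol V2.0 section 13.2 (Planned Analyses). Effects on CRS-R total score "will be further analyzed in subgroups of patients according to their baseline characteristics, i.e., VS/UWS and MCS". The same sentence then names a second factor: "as well as anoxia etiology and non-anoxia etiology".

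The surrounding text adds this:

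- The linear mixed model lists sequence, period, age, etiology and time since injury as fixed effects, with a random subject effect. Baseline diagnosis (VS/UWS or MCS) is not a term, and no interaction is listed.
- The decision rule is general: "Two-sided P-values < 0.05 were considered statistically significant". It is not tied to the subgroups.
- The false discovery rate adjustment is stated in the sentence on EEG analyses. Nothing extends it to subgroups.
- Subgroups have no exploratory label, expected size or power statement. Randomization is "without stratification or blocks", so sequence balance within a subgroup is left to chance.

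The sample size section states that "enrolling 44 patients would provide 90% power to detect a mean difference of 1.2 points (standard deviation [SD] = 1.5"), two-sided alpha 0.05, "accounting for a 15% dropout rate".

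**The concern.** Whether iTBS works differently in VS/UWS and MCS is a question about the difference between two effects. Separate analyses answer two other questions: is there an effect in this subset, and is there one in that subset? Each subset holds only part of a sample sized for the overall effect. One can therefore easily pass the 5% threshold while the other misses it, even when the true effect is the same in both.

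The risk is a claim about which patients respond that rests on contrasting P values. The protocol's own background shows why this matters: it cites a 2014 trial of direct current stimulation that found a benefit in MCS, and a later trial that found none in either MCS or UWS.

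**Working it through.** **Inputs.** From the plan: 44 enrolled, difference 1.2, SD 1.5, two-sided alpha 0.05, 15% dropout, two-period crossover. Not in the documents, so assumed: the subgroup splits and a true effect of exactly 1.2 in every patient.

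**1. Reproduce the planned sample size.** The plan does not say which SD equals 1.5.

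- *SD of each period's change, zero within-patient correlation.* The SD of the within-patient difference is 1.5 × √2 = 2.12. A crossover t-test with n − 2 degrees of freedom needs 35 patients (36 if even) for 90% power. 36/0.85 = 42.4, so 43, or 44 with equal sequences. Conversely, 44 × 0.85 = 37.4; with 37 evaluable, power is 91.7%. This matches the plan.
- *SD of the within-patient difference.* This needs 19 patients; 19/0.85 = 22.4, so 23. With 37 evaluable, power would be 99.7%. It does not match.
- *Parallel groups.* 33 per arm; 66/0.85 = 77.6, so 78. It does not match.

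The main calculation therefore uses 2.12.

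**2. Power within a subgroup.** For a subgroup of n patients, the noncentrality is 1.2√n / 2.12, referred to a noncentral t with n − 2 degrees of freedom. This gives 61.6% for n = 18 and 64.2% for n = 19.

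**3. Probability that exactly one subgroup is significant.** With powers p and q this is p(1 − q) + q(1 − p). For 18/19: 0.616 × 0.358 + 0.642 × 0.384 = 0.221 + 0.247 = 47%.

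| Evaluable | Split | Powers | Exactly one significant |
|---|---|---|---|
| 37 | 18/19 | 62%, 64% | 47% |
| 37 | 15/22 | 53%, 71% | 49% |
| 37 | 11/26 | 39%, 79% | 57% |
| 44 | 22/22 | 71%, 71% | 41% |
| 44 | 13/31 | 46%, 86% | 53% |

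**4. Check that needs no SD.** If the whole trial has exactly 90% power, its noncentrality is 1.96 + 1.2815 = 3.2415. Half the patients give 3.2415/√2 = 2.292, so each half has power Φ(2.292 − 1.96) = 63%. Exactly one significant: 2 × 0.63 × 0.37 = 47%.

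**5. Sensitivity.**

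- SD of the difference 1.5, effect 1.2: 18% at 18/19, 35% at 11/26, 10% at 22/22.
- SD of the difference 2.12, split 18/19, other uniform effects: 9.5% at 0, 33% at 0.6, 13% at 1.8.
- A more uneven split raises the figure: 69% at 7/30 (SD 2.12, effect 1.2).

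**6. The interaction test.** Under a uniform effect it rejects at its nominal level (4.9% to 5.1% in simulation at SD 2.12). Its standard error at 18/19 is 2.12 × √(1/18 + 1/19) = 0.70. With a t quantile of 2.03 on 35 degrees of freedom, the 95% CI is about ± 1.42. Power for a true 1.2-point difference between subgroups is about 39% at 18/19 and 34% at 11/26.

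**The case against.** The plan does not spell out the subgroup method. A reader might infer that it prescribes a separate test in each subset at P < 0.05. It does not: the sentence names no model and no decision rule, and the 5% threshold comes from a general statement. Nor does any objective or outcome concern differential response, and nothing says that significance in one subset will be read as a difference. This stands. The supportable point is that the wording most naturally means separate analyses, and that nothing commits the trial to a comparison or guards against the wrong inference.

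A reader might also infer that a uniform effect would look subgroup-specific about half the time, whatever the circumstances. The documents do not support that unconditionally. They give no subgroup proportions. The 1.2 ± 1.5 wording can be read as the SD of the difference. The main analysis set is all randomized patients with LOCF, not completers. The true effect need not be 1.2.

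Finally, one might object that etiology becomes constant in the anoxic subset, so that the subset models differ. This is immaterial. Etiology is a patient-level covariate, and with both periods observed the treatment contrast is within-patient, so such a covariate does not change it.

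None of this supplies an interaction test, which neither current document contains.

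**Conclusion.** The concern holds as a gap in method. The subgroup analyses as written cannot establish whether the iTBS effect differs by diagnosis or by anoxic etiology, and a standard method that can is available at almost no cost.

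The 41% to 57% range belongs to a stated scenario: uniform effect of 1.2, SD of the difference 2.12, 37 to 44 evaluable patients, splits between 50/50 and 70/30, and a discordant result defined as P < 0.05 in exactly one subgroup. Most of the departures examined lower it; very uneven splits raise it. With the effect at 1.2, even the low figures (10% at 22/22 and 18% at 18/19 under the smaller SD) exceed the 5% of an interaction test.

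The primary estimate, its test and the sample size are unaffected. The change should be made, but it concerns supplementary analyses only.

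**What to change.** In SAP section 6 and protocol section 13.2, replace the subgroup sentence with the following:

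- For each factor, fit one mixed model in all patients with treatment, subgroup and treatment × subgroup, alongside the existing terms. Baseline diagnosis has to be added as a term. For anoxia status, state how the main effect relates to the etiology term already in the model.
- Report the interaction estimate with its 95% CI as the subgroup result. Show within-subgroup estimates with CIs from the same model, without separate significance claims.
- Label these analyses exploratory. State that interaction power is low, about 39% for a 1.2-point difference with 37 patients split 18/19, so that a non-significant interaction is not read as proof of a uniform effect.

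The cost is wording in the two documents. No new data, patients or software are needed.

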## **8.4 EEG recording and analysis**

### **8.4.1 EEG recordings**

EEG signals are recorded using 32 Ag/AgCl ring electrodes connected to an amplifier system (BrainAmp MR Plus, Brain Products GmbH, Gilching, Germany). The electrodes are positioned according to the international 10-20 system. The EEG data acquisition occurs at a sampling rate of 1000 Hz, with impedance kept below 5 k $\Omega$ . EEG data is continuously monitored for 20 minutes, within 30 minutes before and after the first stimulation session, as well as after the fifth stimulation session. Patients are lying on the beds, awake with their eyes open. An arousal-promoting protocol will be implemented if their eyes are closed as previously described.

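### Baseline PSD is undefined in the crossover mixed model, and a single slope for a period-specific baseline would cost precision that splitting it into patient mean and deviation would keep

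*Supplement*

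**What the plan says.** SAP V2.0 section 2.2.2 lists the iTBS-sham difference in PSD after five sessions as a secondary outcome. Section 6 analyses it, and the post hoc comparison after session one, by a linear mixed model, "incorporating baseline PSD as a fixed effect alongside other fixed and random variables as above". Those other terms are sequence, period, time since injury, etiology, age and a random subject effect. Protocol V2.0 section 13.2 has the same sentence.

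Protocol section 8.4.1 gives the recording times: "EEG data is continuously monitored for 20 minutes, within 30 minutes before and after the first stimulation session", and again after the fifth session. SAP section 3 adds: "The two treatment sessions are separated by a 5-day washout period". A baseline recording is therefore available in each period, about 10 days apart (5 treatment days plus 5 washout days). Neither document says that this is the baseline the model uses. Elsewhere they use the word baseline for enrolment or pre-randomisation assessments (protocol section 8.1, SAP section 3).

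The primary CRS-R model uses change scores with no baseline covariate and is not affected.

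**The concern.** In a two-period crossover the treatment effect is estimated within patient. A covariate that varies between periods carries two kinds of information: how patients with generally high power differ from those with low power, and how a patient's own outcome moves when that patient's own baseline moves. For EEG power the first relation is likely to be steep, because differences between patients are stable. The second may be shallow, because the pre-session recording and the one after session five are days apart.

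One coefficient beside a random intercept has to serve both. If it lies well above the within-patient slope, each period's outcome is over-corrected and baseline noise enters the iTBS-sham contrast. A real PSD effect is then more likely to be missed. The covariate was presumably added to gain precision, so the plan should not leave open whether it gains or loses it.

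**Working it through.** **The plan's own figure.** SAP section 4 states that "enrolling 44 patients would provide 90% power to detect a mean difference of 1.2 points (standard deviation [SD] = 1.5", with 15% dropout. Reading 1.5 as the within-patient SD, 36 patients give SE = 1.5 × √(2/36) = 0.354, 1.2/0.354 = 3.39, and power 90.9%. Then 18/0.85 = 21.2, rounded up to 22 per sequence, gives 44. The figure reproduces, but it concerns CRS-R. For PSD the documents give no SD, correlation or power, so every variance below is an assumption.

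**Set-up.** Standardise baseline X and outcome Y to variance 1. Let *a* be the same-period correlation of X with Y, and *c* every cross-period correlation.

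- Within-patient slope (from period differences): βw = (a − c)/(1 − c)
- Between-patient slope (from patient sums): βb = (a + c)/(1 + c)
- The fitted single slope b minimises log Vd(b) + log Vs(b), where Vd = (1 − c) − 2b(a − c) + b²(1 − c) and Vs = (1 + c) − 2b(a + c) + b²(1 + c). It is a weighted mean of βw and βb.
- Variance of the treatment contrast relative to no baseline: single slope 1 − 2bβw + b²; split model 1 − βw².

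The difference between the last two is (b − βw)². In large samples the single slope is therefore never better than the split. It is worse than no baseline only when b > 2βw.

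**Worked case, a = c = 0.7.** βw = 0 and βb = 1.4/1.7 = 0.82. At b = 0.66, Vd = 0.43 and Vs = 0.59, so the weight on βb is (1.7/0.59)/(1.7/0.59 + 0.3/0.43) = 0.81, and 0.81 × 0.82 = 0.66. Single slope: 1 + 0.66² = 1.44. Split: 1.00.

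| a | c | Single vs none | Split vs none | Single / split |
|---|---|---|---|---|
| 0.3 | 0.3 | 1.07 | 1.00 | 1.07 |
| 0.5 | 0.5 | 1.20 | 1.00 | 1.20 |
| 0.7 | 0.7 | 1.44 | 1.00 | 1.44 |
| 0.9 | 0.9 | 1.80 | 1.00 | 1.80 |
| 0.8 | 0.7 | 1.10 | 0.89 | 1.23 |
| 0.8 | 0.6 | 0.84 | 0.75 | 1.11 |
| 0.9 | 0.7 | 0.61 | 0.56 | 1.10 |

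**One pre-study baseline.** X is the same in both periods, its difference is zero, and it drops out of the contrast: ratio 1.00.

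**Simulation at trial size** (44 patients, REML, 1,500 runs, true effect 0.35 SD):

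| a, c | Quantity | None | Single | Split |
|---|---|---|---|---|
| 0.7, 0.7 | SE | 0.117 | 0.142 | 0.118 |
| 0.7, 0.7 | Power | 83% | 69% | 83% |
| 0.9, 0.7 | SE | 0.115 | 0.093 | 0.089 |
| 0.9, 0.7 | Power | 83% | 96% | 97% |

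Mean estimates stayed at 0.35 within simulation error. A patient-level baseline reproduced the no-baseline SE.

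**Other assumed variance structures.**

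- Seven no-carryover settings with 40 patients: the single slope had 3-54% more variance than the split.
- Settings with 37-44 patients, between-patient SD 0.7-1.0 on log power, and fluctuation decaying over 3-7 days: 22-62% more than the split. With a shared period shift instead: 12-70% more. Type I error was near 5% throughout.
- Grid of 175 settings (patient share of variance 0.3-0.9, drift time constant 2-40 days, recording noise). After session five the single slope was worse than no baseline in 157 (ratio 0.84-1.80, median 1.25). After session one it was worse in 95 (ratio 0.01-1.80, median 1.04).

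**The case against.** A reader might infer that the plan forces the between-patient slope onto the treatment comparison and usually makes the PSD test worse than no adjustment. The documents do not support that. They do not say the baseline is period-specific, and one pre-study value does no harm. Even if it is period-specific, the fitted slope is a compromise, though often nearer the between-patient one. Whether it beats no baseline depends on correlations the documents do not give: with a = 0.9 and c = 0.7 the planned model has 39% less variance than no baseline. After session one, where baseline and outcome fall on the same day, the comparison is about even. All of this stands.

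The split has a cost too. If an iTBS effect persists into the period-2 baseline, the larger single slope subtracts part of it and the split subtracts less. For a true effect of 0.30, simulated estimates were 0.274 (split) against 0.295 (single) with 25% persistence. With full persistence they were 0.19 against 0.27 in one set of runs and 0.19 against 0.29 in another. This stands as a named downside. The plan relies on the 5-day washout and has no carryover term, so a sensitivity analysis is a proportionate answer.

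It is also tempting to extend the point to the cumulative link model, which adds baseline ABCD "EEG patterns as fixed effects". That could mean category indicators rather than one slope, no such model was tested, and scoring the patterns 1-4 would impose equal spacing. The extension is not supported.

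**Conclusion.** The point holds in a limited form. The plan leaves baseline PSD undefined. Under one reading the adjustment adds nothing to the precision of the contrast. Under the other, a single slope is less precise than a split baseline, by about 3-60% in variance across most assumed settings, with 70% and 80% at the extremes. For the five-session outcome it is often, but not always, less precise than no baseline; after session one no general statement is possible. The loss is of precision only. These sizes assume no carryover and variance components that are not in the documents.

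The consequence is minor. PSD is secondary in the SAP and is not among the secondary outcomes in the protocol synopsis, and the primary analysis is unaffected. The change is cheap enough to be worth making.

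**What to change.** In SAP section 6 and protocol section 13.2:

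1. Define baseline PSD as the EEG recorded before session 1 of each period.
2. Replace the single baseline term by two fixed effects: the patient's mean of the two period baselines, and the deviation of each period's baseline from that mean.
3. Keep the single-slope model, or a change-score model, as a sensitivity analysis, and say that it is there in case an iTBS effect outlasts the washout.

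Leave the form of the cumulative link model as it is. The cost is one extra model term, a few sentences and one sensitivity analysis; no new data are needed. At 44 patients the extra term was nearly free where it could not help (SE 0.118 against 0.117 with no baseline). The wording should be settled before unblinding.

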## 7 SAFETY ANALYSIS

The primary analysis will be the ITT principle between the assigned treatment groups. The proportion of SAEs between the two groups will be analyzed via generalized estimating equations.  $P < 0.05$  will be statistically significant. Statistical analyses will be performed using the R software (version R4.3.0)

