### **Transcranial magnetic stimulation: a feasible treatment approach**

Transcranial magnetic stimulation is widely considered to be a safe, convenient and effective method to induce excitability changes in brain activity. Repetitive transcranial magnetic stimulation (rTMS) can modulate cortical activity via long-term potentiation and long-term depression to treat neurological and psychiatric disorders, such as Parkinson's disease, stroke, epilepsy, Alzheimer's disease, depression, schizophrenia, etc. In recent ten years, the conscious promoting effect of rTMS in patients with MCS and/or UWS has been tested in clinical trials, mostly targeting the left M1, and the left or right dorsolateral prefrontal cortex (DLPFC) with high-frequency stimulation to produce a brain excitation effect and induce long-term potentiation-like plasticity. M1 and DLPFC seem to have shown conscious restoring efficiency in some trials, but they lack consistent and convincing results in different study populations because the specific mechanism underlying the function is unclear. A recent study showed that rTMS over the posterior parietal cortex (PPC) can be used to treat patients with DoC; however, the efficacy requires further studies. Besides the high-frequency stimulation, iTBS, another more efficient and time-saving stimulation, has been used in a small sample of patients with DoC and resulted in both clinical

behavioral and neurophysiological improvement. Importantly, no serious side effects have been reported in most previous studies.

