## **10.2 Recording and reporting**

Intolerance conditions, as well as seizures, will be dealt with by down-regulating the stimulus intensity, termination of stimulation, or symptomatic management if necessary. During the intervention phase of the study, all SAEs that cannot be excluded as being related to the intervention and intolerance conditions will be collected, fully

investigated, and documented in source documents and CRFs. It is not expected that SAEs related to the intervention will occur after the intervention. In addition, all such events will be reported to the PI and the Data and Safety Monitoring Board (DSMB) as soon as possible (within 24 hours). The DSMB will closely monitor all SAEs for any relationship to the study procedures and protocol and will submit all SAEs to the independent statistician for review.

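### The only safety test in the SAP, a GEE on the SAE proportion, has no zero-event rule; in its usual form (logit link, robust SE) it fails when one or both conditions have no SAE

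*Supplement*

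**What the plan says.** SAP V2.0 section 7 is the whole safety analysis. It sets the population ("The primary analysis will be the ITT principle between the assigned treatment groups"), names the test ("The proportion of SAEs between the two groups will be analyzed via generalized estimating equations"), puts significance at P<0.05 and names R as the software. It gives no link, working correlation, variance estimator, covariates, confidence interval or rule for sparse or zero counts. Other adverse events and intolerance have no named test.

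The trial is a two-period crossover (SAP section 3: "The two treatment sessions are separated by a 5-day washout period") with 44 patients, sized on CRS-R (SAP section 4: "We determined that enrolling 44 patients would provide 90% power to detect a mean difference of 1.2 points", "and accounting for a 15% dropout rate").

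No SAE rate is given. Protocol V2.0 section 10.2 confines collection to the intervention phase and to SAEs whose relation to the intervention is not ruled out. The background says of TMS in this population: "Importantly, no serious side effects have been reported in most previous studies". The chi-square and Fisher sentence is in SAP section 6 (efficacy), beside the baseline comparisons, and is not offered as a safety fallback.

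**The concern.** A robust Wald test from a logistic GEE relies on a normal approximation that needs events in both conditions. With 44 patients, five treatment days per condition and restricted SAE collection, an empty condition is a plausible outcome. The P-value then reflects the fact that one cell is empty, not the evidence that the proportions differ. One SAE under iTBS and none under sham could be reported as highly significant harm, and the reverse as significant protection. If both conditions are empty, the model yields nothing and the SAP offers no other safety statement.

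**Working it through.** **The plan's own figures.** There is none for the safety test. The 44 belongs to the primary endpoint. Taking SD 1.5 in each period with no within-patient correlation, the SD of the difference is 1.5×√2 = 2.12. A crossover t-test then needs N=35 for 90% power, rounded to 18 per sequence; 18/0.85 = 21.2, so 22 per sequence and 44 in total. This reproduces the sample size but says nothing about SAEs.

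**Inputs.** n=44, or about 37 after 15% dropout (44×0.85 = 37.4), and P<0.05, from the SAP. Assumed: logit link, cluster-robust SE, an SAE rate p of 0.5% to 10% that is equal in both conditions, and (first) independent periods.

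**Mechanism.** With k events of n in one condition, the robust variance of its logit is 1/[n·(k/n)·(1−k/n)]. In the empty condition the fitted risk μ tends to 0 and the logit diverges, but its robust variance is nμ²/[nμ(1−μ)]², which tends to 1/n. For 1 versus 0 of 44:

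SE = √(44/43 + 1/44) = √(1.0233 + 0.0227) = 1.02.

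The coefficient grows with each iteration while the SE stays put. After 10 iterations z is already 8.6. At R's stopping point the coefficient is about 17.8 in absolute value, so z is about 17.8/1.02 = 17.4 and P is below 1e-60. Exact McNemar on the one discordant pair gives P=1.00.

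**How often this happens under the null.** With q=(1−p)^n, exactly one condition is empty with probability 2q(1−q), and both with probability q². For n=44:

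| p | q | exactly one empty | both empty (no estimate) |
|---|---|---|---|
| 0.5% | 0.802 | 32% | 64% |
| 1% | 0.643 | 46% | 41% |
| 2% | 0.411 | 48% | 17% |
| 3% | 0.262 | 39% | 7% |
| 5% | 0.105 | 19% | 1% |
| 10% | 0.010 | 2% | <0.1% |

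The maximum is 50%, at p=1.56%. Null simulations with R fits (logistic model with cluster-robust variance, equivalent to GEE with an independence working correlation) rejected in 31–33%, 42–46%, 41–50%, 32–38%, 16–19% and 4% of trials at these six rates. At n=37 one set of runs gave 22%, 34%, 42%, 38%, 23% and 5%, with up to 10% of trials returning no usable variance.

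**Correlation between periods.** The probability becomes 2[(1−p)^n − p00^n], with p00 = 1−2p+p²+ρp(1−p). At ρ=0.3, p=2%, n=44: p00=0.9663, giving 2×(0.411−0.221) = 38%. The maximum over p is 39% at ρ=0.3 and 30% at ρ=0.5.

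**Other versions of the same test.**
- Model-based SE, logit link: P above 0.99 for every table of k versus 0 with k=1 to 5. No inflation, but no sensitivity either.
- Identity link, robust SE, n=44, ρ=0: type I error 0.01%, 0.1%, 1.0%, 2.4%, 5.2% and 7.2% at the six rates.
- A Python GEE routine (independence working correlation): 1 versus 0 gave P=0.32 or about 1e-101 on the same data, depending on which condition was coded as reference. This is numerical breakdown.

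**Exact alternatives.** Exact McNemar had a type I error of 0.0% to 1.8% in the same simulations. With all k discordant pairs in one direction its P is 2×0.5^k: 0.0625 for k=5 and 0.031 for k=6. Its power is about 15% for 2% versus 10%, and 20% for 1% versus 10%. The two-sided 95% Clopper-Pearson upper limit for 0/n is 1−0.025^(1/n): 8.0% for n=44 and 9.5% for n=37.

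**The case against.** **The SAP specifies no link or variance estimator.** A reader might infer that the planned test is invalid in itself. The documents do not support that: the inflation belongs to one configuration, and the two alternatives above do not share it in the rare-event range. But logit with a robust SE is the usual form of GEE for a proportion. Leaving the choice open also allows P near 0 or near 1 from the same table.

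**The SAE rate is assumed.** This stands. The background sentence describes earlier studies. The statement in protocol section 10.2, "It is not expected that SAEs related to the intervention will occur after the intervention", concerns events after treatment, not their frequency during it. The SAE definition is broad and the patients are under neurocritical care. A reader might also infer that the fault holds whatever SAEs are collected. It does not: near a 10% rate the test is about nominal.

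**The percentages vary with software.** They do, and dedicated R GEE packages were not run. The closed form for an empty condition does not depend on software.

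**Safety oversight does not hang on this P-value.** Correct: SAEs go to the DSMB within 24 hours and are assessed for relatedness. A P of 1e-60 from one event would also look absurd. The fault concerns the reported comparison, not patient protection during the trial.

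**Fisher's test is already planned.** Only in the efficacy section, and it is unpaired, so it does not fit the full crossover comparison.

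**McNemar alone would lose patients.** This stands. Protocol section 11.2 ends participation after an SAE judged probably related, so a period-1 SAE can leave no second period. Dropping such patients conflicts with the ITT principle in section 7. The replacement must cover them.

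**Conclusion.** The point holds conditionally. With a logit link and robust SE, and an assumed true SAE rate of 0.5% to 5% per condition with independent periods, the false-positive rate at n=44 is about 18% to 50% instead of 5%. It is lower with within-patient correlation and returns to about nominal near a 10% rate. When neither condition has an event (41% of trials at a 1% rate), no treatment effect can be estimated. Under other unstated choices the inflation disappears, so the SAP's single safety conclusion rests on a decision it has not made. This should be changed: the standard form of the stated method fails in a plausible outcome. Low power for SAEs at this sample size is inherent in a trial sized on CRS-R and is not an analysis error, but it means that a non-significant result cannot be read as safety.

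**What to change.** Amend SAP section 7 as follows.

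- For each condition, report the number and proportion of patients exposed to it who had at least one SAE, with exact (Clopper-Pearson) 95% confidence intervals, including the upper limit when there are no events (8.0% for 0/44, 9.5% for 0/37).
- Replace the GEE Wald P with exact McNemar in patients exposed to both conditions.
- Because patients withdrawn after a period-1 SAE have no second period, add an exact (Fisher) comparison of period 1 by assigned sequence that keeps all randomised patients, or fit a Firth-type penalised model to all exposed periods.
- State that a non-significant P is not evidence of equal safety.

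The cost is SAP wording and a few lines of R, with no new data or patients. The exact tests are conservative, and the model-based period adjustment is lost, although a handful of events could hardly support it.
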